#### Sample size and sequential interim-analysis

Sequential analysis is used to determine the difference in treatment effect on the primary endpoint (see Methods/design section), therefore no fixed sample size estimate can be given [18]. Based on the results of the Dutch retrospective multicentre audit (mortality 25% versus 11%) and PCD results from the literature is anticipated that the minimally invasive 'step-up approach' will reduce the occurrence of the primary endpoint from 45% to 16%. The expected reduction of mortality and morbidity are 10% and 19% respectively. With 80% power at 5% alpha (two-sided) complete data from about 52–77 patients will be necessary to demonstrate this effect, if it truly exists. If no such effect appears, the trial will continue until 88 patients are randomised and available for analysis as 'conventional' sample size calculation with 80% power at 5% alpha (two-sided) would require 88 patients.

Descriptive methods will be used to assess the quality of the data, comparability of treatment groups and endpoints. Continuous sequential analysis will be performed with PEST (PEST 4: user manual. MPS Research Unit (2000), the University of Reading) according to the restricted procedure as described by Whitehead [18]. Every time an endpoint occurs, data management will send a blinded, updated dataset of all included patients to the biostatistician. If one of the boundaries of the sequential analysis plot is crossed during the analysis of the cumulative data, i.e. the difference in treatment is of at least the expected magnitude, the trial steering committee will be informed and will be advised to stop randomising new patients for the trial. The trial steering committee will not be advised to stop early when no relevant differences between the treatments are observed. Next to the primary analysis, the outcome of both groups will also be adjusted forimbalance in presence of preoperative (multi-) organ failure and timing of intervention (after 28 days). These factors, including possibility of performing VARD and the individual components of the primary endpoint will also be included in a multivariate and subgroupanalysis.

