Currently, there are no randomised controlled trials comparing surgical techniques in necrotizing pancreatitis most likely due to low patient volumes, the heterogeneity of the disease and the highly individualized approach. The Dutch Acute Pancreatitis Study Group was founded to resolve several of these problems [24]. Since 2004, 15 of the 20 centres participating in PANTER are also participating in PROPATRIA, a placebo-controlled trial of probiotic prophylaxis in predicted severe acute pancreatitis [25]. Patients who initially are included in PROPATRIA are screened for eligibility in PANTER. Once a patient develops infected necrotizing pancreatitis the outcome for PROPATRIA is reached and he/she can be randomised for PANTER. With this already ongoing multicenter cooperation the logistical and organisational problems are expected to be kept at a minimum.

The sequential analysis of the primary outcome enables us to stop the trial as soon as sufficient evidence has accumulated regarding both clinically relevant and statistically significant treatment difference. Compared to a conventional fixed sample size sequential analysis on average requires less patients to show an expected effect if it truly exists [18]. This can be advantageous when the disorder is as rare as infected necrotizing pancreatitis. Moreover, as soon as the predefined threshold is passed randomisation may seize, thus preventing further patients to be subjected to an inferior treatment. If the presumed effect does not exist, based on conventional sample size calculations, 88 patients will be randomised.

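### Crossing a sequential boundary rejects no difference; it does not show a difference of at least the planned 29 points, as the article says it does

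*Protocol article*

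**What the plan says.** All of this is in the protocol article, mostly under Sample size and sequential interim-analysis.

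- The step-up approach is anticipated to be one that "will reduce the occurrence of the primary endpoint from 45% to 16" per cent. The design has 80% power at two-sided 5% alpha, and Design of study calls the trial a superiority trial.
- The sequential analysis is continuous, in PEST, "according to the restricted procedure as described by Whitehead". On the looks: "Every time an endpoint occurs, data management will send a blinded, updated dataset of all included patients to the biostatistician".
- On sample size: "complete data from about 52–77 patients will be necessary to demonstrate this effect, if it truly exists". Otherwise the trial runs to 88 patients, the conventional figure.
- When one of the boundaries is crossed, the steering committee is told and advised to close randomisation. The article glosses such a crossing, after an i.e., with "the difference in treatment is of at least the expected magnitude".
- The Discussion says that the design lets the trial stop once "sufficient evidence has accumulated regarding both clinically relevant and statistically significant treatment difference".

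**The concern.** The gloss treats a crossing as evidence on the size of the effect. A boundary built for a superiority test at two-sided 5% controls one error: declaring a difference when there is none. The planned 29 points enters only through power, as the alternative that the trial should detect 80% of the time. Power against an alternative does not make a rejection evidence for that alternative.

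At stake is what may be concluded at the moment of stopping. Taken at its word, the clause lets the advice to stop stand as a finding that major morbidity or mortality falls by at least 29 points, when the test has only excluded zero. The risk is greater in a small trial with frequent looks, because the trials that cross early are those whose observed difference is running high.

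**Working it through.** **Inputs from the article.** 45% v 16%; two-sided 5% alpha; 80% power; 88 patients fixed, about 52–77 sequential; a look at each endpoint.

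**Assumed, because the article does not give them.** 1:1 allocation in blocks of 4, outcomes known at once, and the boundary constants.

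**The plan's own figure.** The two-proportion formula with continuity correction gives 45 per arm, 90 in total, within 2 of the stated 88. Fisher exact power at 44 per arm is 79.8%. The 88 is therefore a sample size for testing no difference with 29 points as the alternative.

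**A check that needs no boundary.** In a fixed analysis with 44 per arm, 20 v 11 events gives z = 2.01. The difference is (20 − 11)/44 = 20.5 points, so significance is reached well below 29.

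**Direction.** The article refers to one of several boundaries. A crossing in favour of laparotomy has the opposite sign from the expected effect, so the gloss is false there whatever the constants.

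**Sequential boundaries.** Take Z as the score statistic and V as its information, with symmetric boundaries Z = ±(a + cV). The approximate log odds ratio on the boundary is Z/V = a/V + c. The design value is ln[(0.45/0.55)/(0.16/0.84)] = ln 4.30 = 1.458. Slopes c of 0, 0.25 and 0.5 times 1.458 were taken, and a and the maximum information were solved for 5% alpha and 80% power. Log odds ratio on the boundary at maximum information:

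- A (c = 0): 4.342/4.164 = 1.043, 72% of the design value
- B (c = 0.364): 3.129/4.374 + 0.364 = 1.080, 74%
- C (c = 0.729): 2.149/5.063 + 0.729 = 1.153, 79%

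The observed effect needed to cross late is therefore smaller than the planned one.

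Simulation, 20,000 patient-level trials per scenario, control rate 45%. Crossings are those in favour of step-up:

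| Boundary | Crosses, truth 15 points | Crosses, truth 20 | Crosses, truth 29 | Mean observed difference at crossing, truth 15 | Same, truth 29 | Crossings below 29 points, truth 29 |
|---|---|---|---|---|---|---|
| A | 24.2% | 41.4% | 80.1% | 35.0 | 36.4 | 28.2% |
| B | 25.0% | 42.0% | 80.0% | 37.0 | 37.8 | 25.5% |
| C | 24.0% | 41.3% | 80.1% | 40.5 | 39.7 | 21.2% |

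Mean sample size at 29 points was 57–59, inside the article's 52–77. These runs were ended by information, not capped at 88 patients.

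**With the cap.** Boundary D, Z = ±(2.379 + 0.729V), stopped at 88 patients, crosses in about 72–73% of trials at 29 points, and about 14% of those crossings show less than 29. It crosses in about 20% when the truth is 15 points. When the truth is 45% v 28% (17 points) it crosses in about 25%, with a median observed difference of 37 points.

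At the design rates V ≈ 0.0530n, so on boundary D at 88 patients V = 4.66 and the log odds ratio is 2.379/4.66 + 0.729 = 1.239. That is an odds ratio of 3.45, about 26 points. The unadjusted lower 95% limit is exp(1.239 − 1.96/√4.66) = exp(0.331) = 1.39. At 52 patients V = 2.76, the log odds ratio is 1.592 and the lower limit is exp(1.592 − 1.181) = 1.51. A just-crossing result is thus compatible with effects far below an odds ratio of 4.30.

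**The case against.** The strongest reply is that the clause is a gloss, not the decision rule. The rule is the boundary, its type I error and power are unaffected by how a crossing is described, and the consequence is advice to a committee. That stands, and it limits the point to interpretation.

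A second reply reads the clause as the observed difference. It is then right more often than not: at the design effect, 72–79% of crossings under A–C and about 86% under D show at least 29 points. But the words equate the two without exception, and a high observed difference at crossing is partly produced by the stopping itself. It is about as high when the truth is 15 points as when it is 29.

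Three stronger readings are tempting and not supported:

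- A reader might infer that an inflated, unadjusted estimate will be reported. The article never says so. An estimator that allows for the stopping may well be in the full protocol or analysis plan, and its absence here is no error.
- A reader might infer that the Discussion repeats the 29-point claim. It speaks of clinical relevance and significance but sets no threshold, so it needs at most a matching clarification.
- A reader might infer exact magnitudes. The constants are assumed and the figures move with them: crossing at the design effect is 80% for A–C by construction, but about 72–73% for D once capped at 88. Only the ranges should be used.

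**Conclusion.** The clause is wrong as written. A crossing rejects no difference at two-sided 5%; it does not establish 29 points, and for the boundary favouring laparotomy it cannot. The objections based on the superiority test and on direction rest on the article alone.

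The size of the problem rests on assumed boundaries, 1:1 allocation and immediate outcomes: about 20–25% of trials cross when the truth is 15 points, and about 14–28% of crossings at the design effect show less than 29. The overestimate is an average over trials that cross, not a certainty in any one of them. The conclusion was the same for every boundary tried. This should be corrected because it changes what may be concluded at stopping, but it does not call the stopping rule into question.

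**What to change.** Replace the explanatory clause with: *i.e. the hypothesis of no difference is rejected at an overall two-sided 5% level*. Add one sentence: the size and clinical relevance of the effect are judged from an estimate and confidence interval that allow for the sequential stopping, taken from the sequential analysis already planned. If wished, add a short clarification to the Discussion so that it does not suggest that the boundary itself tests clinical relevance.

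The cost is two sentences. The boundaries, type I error, power and maximum of 88 patients do not change. The only downside is that the reported effect may be somewhat smaller than the unadjusted one.

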#### Data collection

Data are collected via a secured Internet module which was specifically designed for the PANTER trial (Julius Center for primary care and health sciences, UMC Utrecht, the Netherlands). Data are entered online but are not stored on the Internet. Sequential Organ Dysfunction Scores (SOFA) are noted at randomisation [21,22]. The SOFA score, major morbidity (Table 1) and other complications are registered every second day for the first month and twice weekly thereafter until discharge. Furthermore at any (re-)intervention the SOFA score, procedure-related data (length of procedure, blood-loss) and procedure-related complications are scored.

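### Supplementary adjusted and subgroup analyses use timing of intervention, organ failure with no fixed time point and, read literally, the endpoint's own components as factors; values fixed at randomisation should replace them

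*Protocol article*

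**What the plan says.** The section on sample size and sequential interim-analysis makes the sequential comparison of the composite endpoint the primary analysis. It then adds that outcomes will be "adjusted forimbalance in presence of preoperative (multi-) organ failure and timing of intervention (after 28 days"). The next sentence extends the list: "These factors, including possibility of performing VARD and the individual components of the primary endpoint will also be included in a multivariate and subgroupanalysis".

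Other sections bear on when these quantities become known:

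- **Primary endpoint** counts complications after the first intervention that follows randomisation, so that intervention is a post-randomisation event.
- **Inclusion criteria** require that the decision to intervene has already been taken.
- **Randomisation** is stratified by whether a percutaneous drain can be placed through the retroperitoneum, because minimally invasive necrosectomy depends on that route.
- **Data collection** states that "Sequential Organ Dysfunction Scores (SOFA) are noted at randomisation", and that SOFA is scored again at every intervention or re-intervention.

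**The concern.** A covariate or subgroup factor in a randomised comparison should be fixed before allocation can influence it. If the arm shifts the factor and the factor also tracks prognosis, patients with the same factor value are no longer comparable between arms. An adjusted analysis can then show an effect where there is none, or hide a real one. A component of the outcome used as a factor is worse: the model then conditions on part of what it is meant to explain.

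These are the only adjusted analyses that the article names. With at most 88 patients, chance imbalance is plausible, and readers will look to the adjusted results to judge whether the primary finding is robust.

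**Working it through.** **1. Timing of intervention.** The decision to intervene precedes randomisation; the intervention itself does not. The first assigned procedure is a drain in group A and a laparotomy in group B, and the article sets no common interval from randomisation to procedure. The arm can therefore affect which side of day 28 a patient falls on. If timing means timing of surgery, the dependence is built in. In group A surgery follows only after drainage has failed at a 72-hour review, or on deterioration, or never happens, and the Background hypothesises that drainage delays or avoids surgery. The factor is then undefined for patients treated by drainage alone.

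The direction of bias cannot be settled. Suppose, as an assumption, that patients treated later have the better prognosis. An arm whose procedure is systematically later then looks worse after adjustment: its late group takes in patients of intermediate prognosis and its early group keeps the sickest. On the surgery reading the later arm is group A. On the first-procedure reading the article does not say which arm is later, or whether either is. If the arm does not affect timing at all, this bias does not arise.

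**2. Preoperative organ failure.** Two candidate SOFA values exist, one at randomisation and one at the procedure. The analysis text does not choose. The first is a baseline value. The second, if tied to surgery, is measured after active treatment in group A and before any trial procedure in group B.

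**3. Possibility of VARD.** The stratification factor is known before allocation in both arms and is justified by its role in minimally invasive necrosectomy. The analysis text does not say that the two are the same, but they correspond closely.

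**4. Endpoint components as factors.** Inputs from the article: the step-up approach "will reduce the occurrence of the primary endpoint from 45% to 16" per cent, and "The expected reduction of mortality and morbidity are 10% and 19% respectively". These agree: 10 + 19 = 29 = 45 − 16.

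The odds ratio (OR) for the composite is (16/84) / (45/55) = 0.1905 / 0.8182 = **0.233**.

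Now take death as the factor. Every death is an endpoint event, so that stratum has a 100% event rate and says nothing about treatment. Among survivors the event-free percentages stay at 55 and 84, and the events are those with morbidity but no death. The mortality split is an assumption built from the article's figures:

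| Assumed mortality, B to A | Morbidity without death, B | Same, A | OR among survivors |
|---|---|---|---|
| 25% to 15% (audit figure less 10 points) | 45 − 25 = 20 | 16 − 15 = 1 | (1/84) / (20/55) = **0.033** |
| 25% to 11% (audit figures) | 45 − 25 = 20 | 16 − 11 = 5 | (5/84) / (20/55) = **0.164** |

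The same planned effect gives three different odds ratios. The conditional ones compare survivors, a group selected after treatment. They show that the question has changed; they do not estimate bias.

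**5. Sample size.** Not affected. At 45% versus 16%, 80% power and two-sided 5%, with 1:1 allocation assumed, the usual two-proportion formula with continuity correction gives 45 per arm, 90 in total, and Fisher's exact test at 44 per arm has 79.8% power. The article's 88 is thus reproduced closely, and nothing here changes it.

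**The case against.** The strongest reply is that this reads a compressed sentence too literally.

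- **Reach.** The analyses are supplementary: "Next to the primary analysis, the outcome of both groups will also be adjusted forimbalance". The primary comparison is by intention to treat and does not use these factors. This stands. A reader might infer that the trial's main treatment comparison is biased; the article does not support that.
- **VARD.** A reader might infer that feasibility is only discovered at operation, in group A. The article points the other way: the drain route is a stratification factor, an expert panel reviews feasibility on CT before randomisation, and the Discussion reports VARD feasibility judged by re-reading CT scans. The rule for VARD that proves technically impossible governs conversion and does not define this factor. This stands, and only a clearer label is needed.
- **Organ failure.** The article calls the endpoint postoperative in both arms, and its clock starts at the first intervention. Preoperative can likewise mean before the first intervention, which is defined for everyone. This stands as a fair reading, but the text does not fix it and two SOFA values compete.
- **Timing.** The indication is settled before randomisation and no arm-specific schedule is given, so a first-procedure difference may be small. That limits the likely size but does not make the factor a baseline one.
- **Components.** The authors may have meant them as separate outcomes. That is plausible, but the sentence lists them among the factors.
- **Detail left to the analysis plan.** Measurement times often are. Here, however, the article itself names a post-randomisation event as an adjustment factor and puts outcome components among the factors. Those are stated rules.

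**Conclusion.** The point holds for the supplementary adjusted, multivariate and subgroup analyses only. Timing of intervention is realised after randomisation and can differ by arm. Preoperative organ failure is not anchored, although a baseline value is collected. Read literally, the endpoint components enter as factors, which conditions on the outcome. Results from these analyses can be biased or impossible to interpret.

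No size or direction can be given for the bias from timing or organ failure. A reader might want to attach a spurious odds ratio, but that needs an assumed delay between arms and an assumed link to prognosis, and the article supplies neither. The survivor odds ratios of 0.033 and 0.164 rest on assumed mortality splits and illustrate only that a component-conditioned analysis answers another question. Tables 1 and 2, which define the components, were not in the text available, so overlap between preoperative organ failure and an organ-failure component was not checked.

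The correction should be made, but it does not threaten the primary result.

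**What to change.** Reword the two sentences so that every factor is fixed at randomisation:

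- define (multi-)organ failure from the SOFA score at randomisation;
- replace timing of intervention with time from symptom onset to randomisation, using the same 28-day cut or a continuous term;
- state that possibility of performing VARD means the pre-randomisation drain-route stratum;
- analyse the components of the primary endpoint as separate outcomes by arm, and remove them from the covariates and subgroup factors.

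Actual timing of procedures and SOFA at intervention can still be described by arm.

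The cost is wording only. SOFA at randomisation, onset of symptoms and the stratum are already recorded, and the randomisation date should be available from the randomisation module. The sample size and the sequential design do not change.

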#### Feasibility

The recent retrospective survey showed that in a 3-year period 106 patients had undergone surgery for necrotizing pancreatitis in 11 of the 20 participating Dutch hospitals [8]. It is expected that up to 25% of eligible patients will be excluded mainly because of interventions (percutaneous drainage or surgery) being performed prior to randomisation in referring centres. Taking further into account refusal of informed consent (10%), other reasons for drop-out (5%) and loss-to-follow-up (2.5%) it is considered possible to randomise and collect data on 88 patients in 3 years time. After one year, the inclusion rate will be assessed. If accrual is too slow, additional centres will be invited to participate.

### Post-randomisation treatment protocol

All patients receive oral nutrition. If this is not tolerated, a nasojejunal feeding tube is introduced and enteral feeding is started [19]. If gastrointestinal feeding is contra-indicated, the patient will receive parenteral nutrition. Antibiotic treatment, Imipenem-cilastatin therapy 500 mg 3 times daily, is started in all patients with a maximum duration of fourteen days. Antibiotic treatment is switched based on blood cultures and culture from material collected during drainage and/or surgical procedures. If cultures remain negative antibiotic treatment is stopped. Selective decontamination of the digestive tract is allowed.

### Group A: minimally invasive 'step-up approach'

#### Step 1: Drainage

A percutaneous drain (at least 12 French) is placed in the (peri-)pancreatic collection. Multiple drains may be indicated in case of large or multiple collections. The preferred route is through the left retroperitoneum. If this is not possible a transperitoneal route is chosen. A right retroperitoneal route is allowed when it can be safely applied. If this is also not possible, an endoscopic transgastric drainage is performed with two 10 French drains (10 French being the current maximal drain size for endoscopic procedures) including a nasocystic drain for flushing. No continuous lavage system is installed. Drains are kept open by flushing with 50 ml saline once every 8-hrs shift by nursing staff. Extra saline may be used depending on the aspect of the return-fluid, the size of the collections on CECT, communication between drains and connections between collections. If more than 200 ml saline is used daily a drain fluid-balance chart is kept.

If there is no clinical improvement 72 hours after drain placement, this is considered a failure and a CECT is made to check the position of the drain. "Clinical improvement" is defined as: improved function of at least two organ systems (circulatory, pulmonary, renal) within 72 hours, or at least 10% improvement of two out of three parameters: leucocytes/temperature/CRP. If during the repeat CECT the position of the drain is adequate and no additional drainable collections are seen, the patient is taken to the operating room (step two). If the position of the drain is *in*adequate a second drain is placed in the collection.

Seventy-two hours after a second drainage-procedure the patient is again evaluated. In case of improvement, treatment is conservative; otherwise the patient will be taken to the operating room (step two). If after drainage, at any moment in time, a deterioration of at least two organ systems (circulatory, pulmonary, renal), or at least 10% deterioration of two out of three parameters: leucocytes/temperature/CRP occurs, step two is taken. Deterioration (of these parameters) by other infectious causes (e.g. an urinary tract infection) should be excluded.

